### Study participants, study setting and subject eligibility criteria

Children aged 0–6 years and their mothers attending AWCs shall constitute the study population. Expectant mothers and mother-child pair of children aged 0–6 years enrolled at the selected AWCs and who agree to participate in the study will constitute the study sample. Study subjects will be excluded if theyare found to be already enrolled with any other trial related to oral health care.

### Study groups and intervention

#### Group I (intervention group AWC)

Oral Health Care Package (described below) for primary prevention of oral diseases will be delivered to the study participants in this group.

#### Group II (control group AWC)

Participants will receive the standard care, i.e. the routine dental care available at the AWCs. The prevailing standard of oral health care in AWCs is part of maintaining complete hygiene of the body, wherein the AWW gives basic instructions to maintain oral hygiene too.

### Components of Oral health care package

#### Oral health education

Training sessions of 4–5-h duration will be conducted to train AWWs in batches. These sessions will focus on oral health primary preventive strategies using pre-tested standardised oral health education materials (pictorial flip charts, posters, models, pamphlets/brochure in local language) and practical demonstrations on gum pad cleaning, tooth brushing and plaque control using disclosing agents. Pre- and post-training evaluation of the AWWs will be done, and re-training sessions will be conducted for those who fail to reach a cut-off score of 90%. These trained AWWs will then provide oral health education to mothers on (a) proper feeding habits, (b) role of feeding in causation of ECC, (c) oral hygiene measures including gum pad cleaning, (d) types of toothbrushes, their role in maintaining oral hygiene, frequency of brushing per day, time to initiate tooth brushing (e) use of fluoridated toothpaste – its amount, use and frequency (f) role of parents in maintaining oral hygiene of the child, (g) intelligent use of sugars, (h) transmission of S mutans (i) abnormal oral habits, teething, bruxism, dental traumatic injuries etc.

#### Application of 2.26% fluoride varnish and 10% Povidone-iodine

2.26% fluoride varnish and 10% Povidone-iodine will be topically applied to the teeth of children aged 1–6 years, once every 3 months, by a dentist in the same appointment

#### Weekly Oral health education Mobile messages

Mothers, who will subscribe to receiving weekly SMSs, will receive message tips on oral health promotion and disease prevention. These messages will be customised based on the age of the child as well as the presence of risk factors for dental caries and other oro-dental diseases.

### Sample size estimation

Sample size calculation for the study has been based upon a similar study conducted by Lawrence HP et al., 2008 for prevention of dental caries among aboriginal children in Canada, with 2-year, follow up [18]. In the above study, the mean (SD) change of dmfs in intervention and control arm was 11 (14.3) and 13.47 (16.3), respectively, resulting in a mean difference of 2.47.

Assuming a 5% alpha error and 20% beta error, to detect a mean difference with standard deviations as above, using the sample size formula (z_1-α/2_ + z_1-β_)^2^ x (σ_1_^2^ + σ_2_^2^)/(μ_1_-μ_2_)^2^, the required sample size has been calculated to be approximately 605 in each arm. The design effect due to clustering has not been included, because we do not have prior information about the intra-class correlation within a cluster. To account for an attrition in the number of study subjects, and to account for a decrease in the effect size (due to a potential waning in the performance of AWWs in the intervention clusters over the three-year study period, and a possible Hawthorne effect) it was decided to inflate the sample size approximately 1.5 times, resulting in 950subjects in each arm at each study center (Chandigarh and Cuttack). On average, around 25 children are attached to each AWC. Therefore, at each study centre, a cluster of 40 AWCs will be selected within each of the two ICDS blocks, and the blocks will be randomly located to the intervention and the control arm.

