## Methods

### Study design

This will be a pragmatic, two-arm, parallel-group, community-based controlled trial with clusters of AWCs within ICDS blocks as the unit of allocation. Two geographically distant ICDS blocks will be selected at each of the study sites, viz. Chandigarh and Cuttack. The selected blocks will be randomly allocated to the intervention and control group using sealed envelopes by a statistician who will not be the part of this study. AWCs under each of the two selected blocks shall be enumerated and, from them, one AWC will be randomly selected, and further AWCs located adjacent to this AWC will then be chosen so that a cluster of AWCs is formed within the block. This cluster of AWCs will constitute a unit of allocation. A typical cluster-randomised controlled trial should have a large number of small-sized clusters, randomly allocated to an intervention and control arm. However, for logistic reasons, we have opted for a pragmatic design in which only two large-sized clusters at each study centre (Chandigarh and Cuttack) would be compared.

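### The 80% power behind 605 per arm assumes independent children, but the trial allocates four blocks, and nothing in the inflated sample size is set aside for clustering

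*Protocol article*

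**What the plan says.** Under Sample size estimation, the protocol article starts with "Assuming a 5% alpha error and 20% beta error" and takes its inputs from an earlier trial, in which the mean (SD) change in dmfs in the "intervention and control arm was 11 (14.3) and 13.47 (16.3), respectively", "resulting in a mean difference of 2.47". It applies the two-sample formula for independent subjects and reports that "the required sample size has been calculated to be approximately 605 in each arm". On clustering it says: "The design effect due to clustering has not been included, because we do not have prior information about the intra-class correlation within a cluster".

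The number is then raised for other reasons: "To account for an attrition in the number of study subjects, and to account for a decrease in the effect size", the latter through waning performance of the Anganwadi workers and a Hawthorne effect. For these, "it was decided to inflate the sample size approximately 1.5 times, resulting in 950subjects in each arm at each study center". No attrition rate is given. Each block contributes 40 AWCs with about 25 children each.

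Under Study design, allocation is by block: "This cluster of AWCs will constitute a unit of allocation". There are two such clusters at each of two centres, so four in all and two per arm. The same section concedes that a cluster trial would usually have many small clusters, and gives logistic reasons for having few.

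**The concern.** Not knowing the ICC is a reason to show a range. Leaving the design effect out fixes the ICC at its most favourable value, zero. The 80% then belongs to a design with 605 independent children per arm, and the trial does not have that design.

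The inflation does not repair this, because the text spends it on attrition and effect dilution. If the trial ends without a significant difference, readers will judge that result against 80% power, and no sentence in the protocol tells them not to. The Discussion ties wider roll-out to the approach being found effective, so how a null result is read matters.

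**Working it through.** **Inputs from the protocol article.** Two-sided alpha 0.05, power 80%, SDs 14.3 and 16.3, difference 2.47, 950 per arm per centre, 40 AWCs per block, one block per arm per centre. The ICCs are my assumptions; the document gives none.

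**Step 1: reproduce 605.** n = (1.960 + 0.842)² × (14.3² + 16.3²) / 2.47² = 7.849 × 470.18 / 6.1009 = 604.9, so 605. The figure is correct for independent children.

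**Step 2: the inflation.** 950 / 605 = 1.57. This is the whole allowance for attrition, dilution and anything else.

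**Step 3: clustering by AWC.** Children per AWC: m = 950 / 40 = 23.75. Design effect DE = 1 + (m − 1) × ICC; effective n = n / DE; power = Φ(2.47 / √(470.18 / effective n) − 1.96). No losses.

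| AWC ICC | DE | Effective n, one centre | Power, one centre | Effective n, pooled | Power, pooled |
|---|---|---|---|---|---|
| 0.01 | 1.23 | 774 | 89% | 1,548 | 99% |
| 0.02 | 1.46 | 653 | 83% | 1,306 | 98% |
| 0.03 | 1.68 | 565 | 77% | 1,129 | 97% |
| 0.05 | 2.14 | 444 | 67% | 889 | 92% |

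The ICC at which power falls to 80% is (950/605 − 1) / 22.75 = 0.025 for one centre, and (1,900/605 − 1) / 22.75 = 0.094 pooled.

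**Step 4: clustering by block, pooled.** With two blocks of 950 per arm, the variance of the difference is (470.18 / 2) × [ICC + (1 − ICC) / 950]. Power is given by normal approximation and by the non-central t with 4 blocks − 2 arms = 2 degrees of freedom (df), critical value 4.30.

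| Block ICC | DE (m = 950) | SE of difference | Power, normal | Power, 2 df |
|---|---|---|---|---|
| 0 | 1.00 | 0.498 | 99.9% | 71% |
| 0.001 | 1.95 | 0.695 | 94.5% | 49% |
| 0.005 | 5.75 | 1.192 | 54.4% | 23% |
| 0.01 | 10.49 | 1.611 | 33.5% | 15% |

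If centre is also fitted as a stratum, 1 df remains and the last column becomes about 30%, 22%, 13% and 10%. By normal approximation, pooled power falls to 80% at a block ICC of (1,900/605 − 1) / 949 = 0.0023.

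**Step 5: would more children help?** As the number of children per block grows without limit, the variance tends to (470.18 / 2) × ICC. At a block ICC of 0.01 power then tops out at about 36% (normal) or 16% (2 df). The number of blocks is the limit.

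**Step 6: cluster size in the primary cohort.** The primary analysis uses only children aged 1 to 3 at entry, and the article does not say whether the 25 per AWC are all of that age. If, as an assumption, 15 were, n would be 40 × 15 = 600 per arm per centre. DE at ICC 0.01 and 0.05 would be 1.14 and 1.70. Power would be about 74% and 57% in one centre (effective n 526 and 353), and about 96% and 86% pooled (1,053 and 706).

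**The case against.** The strongest reply is pooling. The protocol sets 950 per arm at each centre, its Plan for analysis describes one inter-group comparison without splitting it by centre, and no sentence claims 80% power within a centre. This stands for AWC-level clustering: 1,900 per arm keeps 92% to 99% power over ICCs of 0.01 to 0.05 before losses. A reader might infer from the one-centre figures that the whole trial is underpowered because of similarity within AWCs. The documents do not support that. Pooling does not answer the block level, because it leaves two allocated units per arm.

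The second reply is disclosure. The article admits the omission and the small number of clusters, so readers are not misled about the design. That is fair, but 605 at 20% beta remains the stated basis of the sample size, with no statement that the power does not carry over.

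Three further inferences fail:

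- That 605 is miscalculated. It reproduces exactly; the fault is an omitted term.
- That block-level power can be quoted within one centre. With one block per arm there are no degrees of freedom to estimate between-block variance, so such a figure has no test behind it.
- That the true power is known to be low. It depends on ICCs that the documents do not give, and at a block ICC near 0.001 the normal approximation still gives about 94%.

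**Conclusion.** The concern holds in a limited form. The 80% is the power of an individually randomised trial, and nothing in the inflated number is reserved for clustering. Within one centre, an AWC ICC of 0.025 uses up the whole inflation. Over both centres the AWC level is not the problem; the block level is. With four blocks and 2 df, 80% is not reached at any block ICC, and power drops to 49% at 0.001 and 15% at 0.01.

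These figures assume the design difference of 2.47, the SDs in the protocol, m = 23.75 or 950, and no attrition or dilution. The protocol expects both of those, so power would be lower. The point needs correcting because the stated power is one that the allocated design does not have, and restating it is cheap.

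**What to change.** In Sample size estimation:

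1. State that 605 per arm and 80% power assume independent children.
2. Replace the single 80% with a table of power or detectable difference: per centre for AWC ICCs of 0.01 to 0.05, and pooled for AWC ICCs of 0.01 to 0.05 and block ICCs of 0 to 0.01 with 2 df. Use the expected number of 1 to 3-year-olds per AWC, and label every ICC as an assumption.
3. State that 80% power is not claimed for block-level inference with four blocks, that the block rows show sensitivity only, and that a null result must be read accordingly.
4. Baseline dmfs may inform the AWC-level ICC, but only as a proxy, because the primary outcome is change in dmfs. Update the table with the ICC of change, estimated within blocks and blind to arm. Four blocks cannot usefully estimate a block ICC, so those rows stay assumed.

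Recruit no more children; Step 5 shows that this would not restore block-level power. The cost is a paragraph, a table and one blinded estimate, and a less favourable power statement. Recruitment, treatment and visits do not change.

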### Plan for analysis

As the population of children in an AWC is not stable, with older children who cross 6 years of age leaving the AWC and young children joining the AWC; two types of analysis have been planned. The primary analysis will be an inter-group comparison of a stable cohort of children aged 1 to 3 years who will be recruited at the beginning of the study and shall be followed up for 3 years until the age of 4 to 6 years respectively. The secondary analysis will be a cross-sectional inter-group comparison of all available children aged 1 to 6 years present at follow up evaluations (6 months, 1 year, 2 year and 3 years). Children in the secondary analysis will have varying points of entry and different durations of follow-up. All the above-listed outcome variables will be analysed both in the primary and the secondary analysis.

The primary analysis will be done on an intention-to-treat basis. Qualitative data shall be expressed using frequency distribution and percentages, whereas quantitative data shall be expressed as mean (standard deviation) or median (1st, 3rd quartile) depending upon distribution. Normality of distribution will be assessed by Shapiro Wilk test and Q-Q plot. Qualitative variables will be compared between the two groups by chi-square test or Fisher’s exact test, as appropriate. Quantitative variables will be compared between the two groups by Student’s t-test or Mann-Whitney U test, depending upon distribution. Repeated measures analysis between the two groups will be performed using two-way repeated-measures ANOVA or mixed linear models or generalised estimating equations, depending upon the variable and statistical assumptions.

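### The 40 AWCs per arm per centre are derived from all attached children, while the primary cohort is only those aged 1 to 3, so the stated 950 is not secured for the primary outcome

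*Protocol article*

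**What the plan says.** Under Sample size estimation, the protocol article takes its planning values from an earlier caries-prevention trial, in which "the mean (SD) change of dmfs in intervention and control arm was 11 (14.3) and 13.47 (16.3), respectively", "resulting in a mean difference of 2.47". At two-sided 5% alpha and 20% beta, "the required sample size has been calculated to be approximately 605 in each arm". For attrition, and for a weaker effect over three years, "it was decided to inflate the sample size approximately 1.5 times", which the article carries to 950 per arm at each of the two centres. No design effect is included. The number of Anganwadi centres follows at once: "On average, around 25 children are attached to each AWC. Therefore, at each study centre, a cluster of 40 AWCs will be selected" in each of the two blocks.

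The population for the primary outcome is narrower than the population of an AWC. Outcome variables defines the primary outcome as change in dmfs in children aged 1 to 3, and Plan for analysis says: "The primary analysis will be an inter-group comparison of a stable cohort of children aged 1 to 3 years", followed for three years. All available children aged 1 to 6 form a separate, secondary analysis. The eligibility section is wider still: "Children aged 0–6 years and their mothers attending AWCs shall constitute the study population". The Background describes AWCs as serving children under 6.

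**The concern.** The target of 950 is a number of primary-outcome children. The divisor of 25 is, as printed, a number of children of any age on an AWC's books. Dividing one by the other gives the right number of AWCs only if nearly every attached child is aged 1 to 3. An AWC that keeps children until they pass 6 is unlikely to have that mix.

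If the mix is more ordinary, the primary cohort is well short of 950 per arm per centre from the first day. The 1.5-fold allowance for attrition and a diluted effect would be used up before any child is lost. A null primary result, above all within one centre, would then be hard to tell apart from a cohort that was too small.

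**Working it through.** **Inputs from the documents.** SDs 14.3 and 16.3, difference 2.47, alpha 5% two-sided, power 80%, inflation of about 1.5, target 950 per arm per centre, 25 children per AWC, 40 AWCs per arm per centre (all Sample size estimation); primary cohort aged 1 to 3 (Outcome variables; Plan for analysis).

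**Assumptions.** The share of attached children aged 1 to 3 is not given. With an even age spread, the band covers two or three single-year ages, out of six (under 6) or five (1 to 6). That gives 2/6, 2/5, 3/6 and 3/5, or 33%, 40%, 50% and 60%. The five-year denominator is the choice more favourable to the plan. A loss of 20% is also an assumption.

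**Step 1: the plan's own figure.** n = (1.960 + 0.8416)² × (14.3² + 16.3²) / 2.47² = 7.849 × 470.18 / 6.1009 = 604.9. The stated 605 per arm is reproduced.

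**Step 2: inflation and conversion.** 605 × 1.5 = 907.5; the stated 950 is a factor of 950/605 = 1.57. Then 950/25 = 38, taken up to 40, and 40 × 25 = 1,000 attached children.

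**Step 3: share needed.**
- For 950 aged 1 to 3 per arm per centre: 950/1,000 = 95% of attached children.
- For the uninflated 605 per centre: 605/1,000 = 60.5%, with no loss at all.
- For 605 per arm pooled over two centres: 605/2,000 = 30.3% before loss.
- For 950 per arm pooled: 950/2,000 = 47.5%.

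**Step 4: cohort size and power.** Power = Φ(2.47 / √(470.18/n) − 1.96), with n children per arm. Example for 333 per arm: √(470.18/333.3) = 1.188; 2.47/1.188 = 2.08; 2.08 − 1.96 = 0.12; Φ(0.12) = 0.548.

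The last column lets the whole inflation allowance go to attrition, a loss of 1 − 605/950 = 36.3%. This is severe, because part of that allowance was meant for a smaller effect.

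| Share aged 1 to 3 | n per arm per centre | Power, no loss | Power, 20% loss | n per arm pooled | Power, no loss | Power, 20% loss | Power, 36.3% loss |
|---|---|---|---|---|---|---|---|
| 33% | 333 | 54.8% | 46.0% | 667 | 83.7% | 74.9% | 65.1% |
| 40% | 400 | 62.5% | 53.1% | 800 | 89.7% | 82.2% | 72.9% |
| 50% | 500 | 72.1% | 62.5% | 1,000 | 95.0% | 89.7% | 82.0% |
| 60% | 600 | 79.7% | 70.4% | 1,200 | 97.6% | 94.2% | 88.3% |

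Every per-centre count lies below 605, at the top of the range by only five children. All these powers ignore clustering, as the plan does, so true power is lower throughout.

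**The case against.** Four points can be made for the plan.

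**The 25 may already be age-restricted.** The article says only that the children are attached to the AWC. The Background gives a catchment of 1,000 people per AWC (700 in tribal regions), so 25 children would be 2.5% of it (25/700 = 3.6%). If each single year of age held 1.5% to 2.5% of the population (an assumption), a catchment of 1,000 would hold 30 to 50 children over two year-bands and 45 to 75 over three. On that footing 25 is some subset. An age-restricted subset would close the gap; an attendance or enrolment subset of all ages would not. The documents do not settle which, so the shortfall must stay conditional.

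**Power may be meant for the pooled trial.** A reader might infer that the trial has lost its 80% power outright. The documents do not support that. The 80% is attached to 605 per arm, and the centre appears only when 950 is stated. The objective in the Abstract compares package with usual care across both sites, and the Background presents comparison between the sites as an addition. On the pooled reading, the cohort exceeds 605 per arm at every assumed share before loss, and power falls below 80% after 20% loss only near the low end. This stands. Against it, 950 is stated per arm per centre, and the article never says that the primary comparison is pooled.

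**No calculation is wrong.** True: 605 reproduces, and 1,000 covers 950. The fault is that the two sides of the conversion count different children.

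**An article may leave register counts to the full protocol.** It may. But this article prints the whole chain from 605 to 40 AWCs and joins its last step with a therefore. On the natural reading that step does not follow for the primary cohort, and a separate analysis plan would not change how many AWCs are selected.

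**Conclusion.** The conversion from 950 children to 40 AWCs is wrong as written for the primary outcome. On the natural reading of the 25, and with an even age spread, the primary cohort is about 333 to 600 per arm per centre. That is 35% to 63% of the stated 950 (333/950 and 600/950), and from just under to well below the uninflated 605.

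The consequence for power depends on a choice the article does not state. Per centre, power is about 55% to 80% before loss and 46% to 70% after 20% loss. Pooled, it is 84% to 98%, 75% to 94%, and 65% to 88% if the whole allowance is lost. The firm conclusion is therefore that 950 primary-cohort children per arm per centre are not secured, and that per-centre power is probably below 80%. It is not established that a pooled primary test is underpowered on the plan's own individual-level terms. The conclusion rests on the age band behind the 25, the assumed even spread and the assumed losses. If the 25 means children aged 1 to 3, it falls away.

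**What to change.** Count the children aged 1 to 3 in the registers of the selected AWCs, and state the exact age limits used. Then, in Sample size estimation:

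- give that count as the expected primary-cohort size, per arm per centre and pooled;
- restate the power for 2.47 dmfs, or the detectable difference, for that size after the expected attrition;
- say whether the primary test and its 80% power apply per centre or to both centres pooled with stratification by site;
- unless the registers show otherwise, describe 950 to 1,000 as all attached children, with the age band as registered, and not as the primary cohort. Labelling it the sample aged 1 to 6 would be unsafe too: if the 25 covers ages 0 to 6, an even spread gives only 1,000 × 5/6 = 833 aged 1 to 6.

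Whether more AWCs are needed cannot be decided before the count. For scale, 950 children aged 1 to 3 per arm per centre would take 950/(25 × share), or about 115, 95, 76 or 64 AWCs at shares of 33%, 40%, 50% and 60%.

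The cost is a register count and one rewritten paragraph. The downside is that the stated size and power will look less favourable, especially per centre.

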### Plan of study (Fig. 1)

#### Measurement of variables

The following demographic variables and potential confounders will be recorded at enrollment; socio-economic status of children, number of siblings, order and age of children, child anthropometry (weight & BMI), eating patterns, oral health services utilisation by children and health behaviors of children, maternal and child medical history and health literacy levels of mothers etc.

